### 2.8. Statistical Methods

Statistical analyses will be conducted adopting both a frequentist and a Bayesian approach to provide robust evidence favoring or against the intervention.

The main study outcome is to verify the effectiveness of the intervention: this would be verified by a T0 to T1 delta different from 0. Additionally, we will test the effectiveness of the IB-MAI against the CC group comparing the two T0 to T1 deltas. We will use a series of *t*-tests and its Bayesian [83] corresponding test.

Stability over time will be verified with a mixed ANOVA using the T1, T2 and T3 datapoints as within-subject measures and group (IB-MAI versus CC) as a between-subjects factor. We will use “classic” (i.e., frequentist) ANOVA and its corresponding Bayesian version [84] for each primary and secondary outcome measure.

For what concerns the predictive model, we will explore the possibility to use ML algorithms to tune a model able to predict the responders on each of the primary outcomes starting from the socio-demographic information collected and the primary and secondary outcome measures in two steps. First, we will use only socio-demographic information to predict the primary outcome measure of each module. Second, we will use the socio-demographic information, the other primary, and all the secondary outcome measures to predict the primary outcome of each specific module. Before entering an outcome measure as a target variable (i.e., to be classified/predicted variable), variables have to be dichotomized. We will classify participants as responders or non-responders, adopting the minimum clinical importance difference and adopting a distribution approach [85]. A responder will be defined as a participant that records a change larger than 1 standard error of the mean (SEM) calculated on the baseline distribution. For example, the effectiveness of the first module is measured primarily on the BDI-II scale. We will first identify participants that change more than 1 SEM to classify responders and non-responders. Then we will use ML algorithms to predict this outcome starting from socio-demographic in a first step, and socio demographic plus the other outcome variables (except BDI-II of course) in a second step. We will test five different algorithms to have a good mixture of simple linear (LDA), nonlinear (CART, kNN), and complex nonlinear (SVM, RF) methods, thus covering the most used and diffused ML methods [86]. A total of 20% of the data will be held out for testing purposes, thus ML training will be performed on the remaining 80% data of the total sample. The portion of sample holdout will be set at the beginning and kept constant for all the algorithms tested and outcomes targeted, to make the different models’ performances directly comparable.

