### Aims and Hypotheses

MindBlooming is a two-year research project with multiple primary goals and related hypotheses. Firstly, we aim to design and implement a new Internet-Based Multi-Approach Intervention (IB-MAI) for university students. The intervention covers a wide range of mental health issues that are relevant within the university student population [11,28] and that are treatable with IBIs [23,25,29]. Furthermore, the intervention is tailored to the individual’s needs. The mental health issues that MindBlooming addresses are depression, anxiety, sleep problems, self-disruptive thoughts, job- and study-related stress and burnout, and chronic pain.

Secondary aims will be: (1) the feasibility assessment of this IB-MAI (in terms of acceptability, satisfaction, usability, and uptake) through a pilot study on a restricted sample; (2) a randomized controlled trial (RCT) to compare the IB-MAI with web-education, as the control condition (CC); and (3) exploratory analysis to tune a predictive model on the collected data adopting Machine Learning techniques.

We hypothesize that: (1) the design and implementation of the IB-MAI treatment will be feasible; (2) the majority of the students will accept and be satisfied with the treatment; (3) the IB-MAI will be superior to the CC on both the primary and secondary outcome measures; and (4) the large amount of collected data will allow the identification of predictors of treatment response and different trajectories in treatment response.

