### 2.7. Sample Size Calculation

Considering the attrition rate, we will recruit 260 students to obtain 200 study completers. A total of two-hundred participants will allow to detect an effect size of at least d = 0.40, fixing a power (1 − β) of 80%, and an alpha of 0.05 (two-tailed) in a between group comparison (e.g., comparing the two treatments). This sample size is similar to Harrer et al. [25]. The effect size is estimated considering a recent meta-analytic review for Internet-based stress interventions which reports effect sizes ranging between d = 0.32 and d = 0.64 [81].

Frequentist and Bayesian approaches have their own advantages and drawbacks in data analysis. We will adopt both to provide robust evidence to the specific statistical approach.

We conducted a Bayes Factor Design Analysis (BFDA) [82] (i.e., the counterpart of power analysis in the Bayesian world) to estimate the Bayesian analysis sensitivity, given the sample size of 200 people. We simulated 10,000 results, fixing the Bayes Factor (BF) decision boundary at 10, and an estimated effect size for a true H1 equal to d = 0.40. The BFDA simulation was performed for a default prior (i.e., a Cauchy distribution with a scale = 0.707) and an informative prior (i.e., a t distribution with μ = 0.35, df = 3, r = 0.102), considering true H0 (i.e., d = 0) and H1 (d = 0.40). Given those parameters, we estimate to surpass the decision boundary for H1 in 87.8% adopting the default prior and 93.8% of the case adopting the informed prior. In the case of a true H0, the decision boundary is surpassed in 45.5% and 62.2% of the cases adopting the default or the informed prior, respectively. The design is robust to the misleading evidence, showing a false positive evidence rate of 0.002 and 0.006 adopting the default or the informed prior. No false negative evidence has been observed over 10,000 simulations with any of the two priors. In the case of inconclusive evidence, we will increase the sample size until the BF decision boundary is surpassed (BF > 10) in either one of the two directions supporting H1 or H0.

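### Section 2.8 lets a T0-T1 change with no control term decide effectiveness and makes the randomised comparison additional, against hypothesis 3 and the sample size basis

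*Protocol article*

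**What the plan says.** Section 2.8 (Statistical Methods) makes effectiveness of the intervention the main study outcome and states the decision rule for it: "this would be verified by a T0 to T1 delta different from 0". The next sentence brings in the control arm: "Additionally, we will test the effectiveness of the IB-MAI against the CC group comparing the two T0 to T1 deltas". Both are to be tested by t-tests and their Bayesian counterparts. Because the comparison of the two arms' deltas is listed separately, the delta in the first sentence cannot itself be the between-arm difference. The section does not say whether that delta is taken in the IB-MAI arm or over both arms together.

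Other sections point to the randomised comparison:

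- Aims and Hypotheses gives the purpose of the RCT as comparing IB-MAI with web-education. Hypothesis 3 is that "the IB-MAI will be superior to the CC on both the primary and secondary outcome measures".
- Section 2.7 fixes 80% power and a two-tailed alpha of 0.05 "in a between group comparison (e.g., comparing the two treatments").
- The Discussion says that the treatment will be compared with a control condition.

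**The concern.** A pre-post change in one group mixes any treatment effect with everything else that moves scores over the treatment period. Under section 2.1, students enter because they declare symptoms. Outcomes are self-report questionnaires completed repeatedly. Regression to the mean, time effects and expectancy can therefore shift the scores with no specific effect of the app, and the randomised control arm exists to remove these influences.

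The rule as written does not use that arm. If both arms improve equally, section 2.8 would count effectiveness as shown while hypothesis 3 fails. The article does not say which of the two results would then be the trial's conclusion, so its headline claim is at stake.

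**Working it through.** **Inputs.** From section 2.7: d = 0.40, power 80%, two-sided alpha 0.05, 260 recruited, 200 completers. From section 2.3: 1:1 allocation, 130 per arm. Taken from these: about 100 completers per arm, with attrition of 60/260 = 23.1%. Assumed, because the article gives no figure: a non-specific T0-T1 change of 0 to 0.5 SD of the change score, equal in both arms, and no treatment effect.

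**1. The plan's own figure.** For two means, n per arm = 2(1.960 + 0.842)² / 0.40² = 98.1, so 99 per arm or 198 in total, against the stated 200. With 100 per arm, the noncentral t-distribution (198 degrees of freedom, noncentrality 0.40 × √(100/2) = 2.83) gives power of 80.4%. The stated sample size reproduces, and it reproduces as a between-group calculation.

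**2. The main criterion of section 2.8 when there is no treatment effect.** A one-sample t-test on the change, with n people and a standardised non-specific change δ, has noncentrality δ√n. For n = 100 and δ = 0.2 this is 2.0, against a critical value of 1.98, so the test rejects in about half of trials. Rejection probabilities in full:

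| Non-specific change δ (SD of change) | 100 in IB-MAI arm | 130 in IB-MAI arm | Both arms pooled, 200 |
|---|---|---|---|
| 0 | 5.0% | 5.0% | 5.0% |
| 0.1 | 16.8% | 20.5% | 29.1% |
| 0.2 | 50.8% | 61.9% | 80.4% |
| 0.3 | 84.4% | 92.4% | 98.8% |
| 0.4 | 97.7% | 99.5% | >99.9% |
| 0.5 | 99.9% | >99.9% | >99.9% |

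The CC arm, tested in the same way with the same number of completers, would meet the criterion just as often.

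**3. The between-arm comparison of deltas.** A change common to both arms cancels in the difference. In 20,000 simulated trials at each δ from 0 to 0.5, with 100 per arm, the two-sample t-test on change scores rejected in 4.7% to 5.2% of trials.

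**The case against.** The strongest reply is that the randomised comparison is not missing. Section 2.8 commits to it in the very next sentence, section 2.7 powers it, and hypothesis 3 rests on it. A reader of the results would see a null difference between arms beside any pre-post change. This stands, and it limits the point to one of hierarchy. A reader might infer that the trial makes no use of its control arm, or has essentially no protection against a false claim. The article does not support that: the first is true of one sentence only, and the second depends on an assumed drift. The error rate is 5% at zero drift and about 17% at 0.1 SD.

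The figures also cover only the frequentist test, whereas the plan adds a Bayesian one with a Bayes factor boundary of 10. For a one-sample test with n = 100 and the default Cauchy prior (scale 0.707, two-sided), the chance of passing that boundary is about 14%, 46% and 81% at drifts of 0.2, 0.3 and 0.4 SD. These are lower than 51%, 84% and 98% but still well above 5%. The article does not say that both approaches must agree before effectiveness is concluded, so this qualifies the size of the problem without removing it.

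Finally, a reader might infer from the lack of direction in the criterion that worsening would be counted as effectiveness. That is over-literal: two-sided testing is ordinary, direction is read from the estimate, and the test in section 2.7 is two-tailed too. The point does not rest on it.

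**Conclusion.** The point holds as an error in which test decides. Section 2.8 gives the main role to a criterion without a control term, in conflict with hypothesis 3 and with the basis of the sample size. This is a stated decision rule, not a detail left to a fuller document.

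Followed literally, the rule raises the chance of a false declaration from 5% to 17%, 51%, 84% or 98% at a non-specific change of 0.1, 0.2, 0.3 or 0.4 SD of the change score. These figures assume 100 IB-MAI completers, testing in that arm alone, the frequentist t-test and a drift that the article does not quantify. The conflict between the sections rests on none of these assumptions. It should be corrected before analysis because it governs the trial's main conclusion.

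**What to change.** Replace the two sentences in section 2.8 by a rule of this kind: effectiveness is concluded only from the comparison of T0-T1 deltas between IB-MAI and CC on the primary outcome measures of section 2.6.1, at two-sided alpha 0.05 and with the difference favouring IB-MAI; T0-T1 changes within each arm are reported descriptively with confidence intervals and carry no claim of effectiveness. The Bayesian counterpart should follow the same order.

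Keeping the comparison on deltas leaves the planned between-arm analysis as it is. The cost is a rewording: no extra data and no extra participants. The planned 200 completers give 80.4% power at d = 0.40, reading d in SDs of the change score, a scale that section 2.7 does not specify.

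Section 2.6.1 lists several primary measures, not one. How a conclusion is drawn across them is a separate multiplicity issue, which this rewording does not settle.

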### 2.3. RCT Design

This study will be conducted in accordance with the Consolidated Standards Of Reporting Trials (CONSORT) checklist for the RCT design [34]. Participants will be randomly assigned following blind simple randomization procedures when they complete the baseline assessment (randomization sequence under computer control adopting computerized random numbers) to 1 of 2 treatment groups (see Figures S1 and S2 for the study design and assessments). We only keep the 1:1 ratio constraint at the 260th participant, meaning that when one group reaches 130 participants, all the remaining volunteers (up to the total of 260) will be allocated to the other group. Students will be randomized to IB-MAI or CC. Participants in the intervention condition will receive an 8-week unguided IB-MAI program, i.e. MindBlooming. Participants in the CC condition will access websites with information about their specific areas of distress identified at baseline. Participants will be assessed with repeated measures (baseline, 8 weeks, 12 weeks, and 24 weeks). The RCT participants’ flow is presented in Figure 2.

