### 2.6. Outcome Measures

Participants will be screened with a complete online battery to assess their symptoms, including both primary and secondary outcome measures, at pretreatment baseline (T0), after the 7-week IB-MAI treatment, or CC completion (T1), at 12-week follow-up (T2), and 24-week follow-up (T3) (see Figures S1 and S2 for the study design and assessments). Moreover, at pretreatment time (T0), socio-demographic questions are included; these concern marital status, educational qualification, employment status, physical or psychiatric illnesses, and past or current therapies. Questions related to gender and the COVID-19 pandemic are included to investigate the influence of the pandemic on students’ mental health status. These items were drawn up according to the International COVID-19 Suicide Prevention Research Collaboration guidelines [56]. In contrast, those relating to gender were taken from the Williams Institute of the UCLA School of Law for health surveys [57].

Since participants have a timeframe to begin and complete each week of treatment, the overall treatment duration can differ among subjects. Therefore, post-treatment and follow-up time points will be calculated for each participant, starting from the end of the last activity.

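### The between-arm t-test on raw T0–T1 change scores is valid but gives away precision that an ANCOVA on the T0 score would recover from data already collected

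*Protocol article*

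**What the plan says.** Section 2.8 takes as the main question whether the T0-to-T1 change differs from zero. It then turns to the comparison of arms: "Additionally, we will test the effectiveness of the IB-MAI against the CC group comparing the two T0 to T1 deltas". The method is stated: "We will use a series of *t*-tests and its Bayesian [83] corresponding test". For follow-up it says: "Stability over time will be verified with a mixed ANOVA using the T1, T2 and T3 datapoints as within-subject measures", with arm as the between-subjects factor, in frequentist and Bayesian form, for each primary and secondary outcome. T0 is a covariate in neither analysis.

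The T0 scores will exist. Section 2.6 describes a full battery, "including both primary and secondary outcome measures, at pretreatment baseline (T0"), repeated at T1, T2 and T3. Section 2.3 places allocation after that assessment: "Participants will be randomly assigned following blind simple randomization procedures when they complete the baseline assessment".

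Section 2.7 sizes the trial at 260 recruited and 200 completers, for d = 0.40 with 80% power and "an alpha of 0.05 (two-tailed) in a between group comparison". It does not say whether d is standardised by the SD of the score or by the SD of the change.

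**The concern.** Subtracting the T0 score amounts to assuming that each point at baseline carries forward as one full point at T1. Questionnaire scores usually regress toward the mean, so the true slope is usually below 1 and the subtraction over-corrects. With equal SDs and rho below 0.5, the change score is noisier than the T1 score alone. ANCOVA estimates the slope instead of fixing it.

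The superiority hypothesis in Aims and Hypotheses rests on this between-arm comparison. Section 2.7 also says that the sample will be enlarged if the Bayes factor is inconclusive. A noisier contrast makes that outcome more likely when there is a true effect, so lost precision could turn into extra recruitment.

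**Working it through.** **Inputs from the article:** 200 completers (taken as 100 per arm from the 1:1 ratio), d = 0.40, two-sided alpha 0.05, power 80%.

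**Assumed:** equal SD at T0 and T1; rho of 0.3, 0.5 and 0.7, with 0.8 as a favourable extreme. None of these is in the article.

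**1. The plan's own figure.** A two-sample comparison at d = 0.40 needs 99 per arm, 198 in total, against 200 stated. Power at 100 per arm is 0.807 by the normal approximation and 0.804 with the t distribution. The stated sample size reproduces.

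**2. Variances, in units of the score variance.**
- Change score: 2(1 − rho)
- ANCOVA: 1 − rho²
- Ratio ANCOVA/change: (1 − rho²) / [2(1 − rho)] = (1 + rho)/2

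The ratio is 0.65, 0.75, 0.85 and 0.90 at rho 0.3, 0.5, 0.7 and 0.8. Taking square roots, ANCOVA confidence intervals are about 19%, 13%, 8% and 5% narrower.

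**3. Power at 100 per arm (normal approximation).** If d is on the score SD, the effective d is 0.40/√[2(1 − rho)] for the change score and 0.40/√(1 − rho²) for ANCOVA. If d is on the change SD, it is 0.40 for the change score and 0.40/√[(1 + rho)/2] for ANCOVA.

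| rho | d on change SD: change score | d on change SD: ANCOVA | d on score SD: change score | d on score SD: ANCOVA |
|---|---|---|---|---|
| 0.3 | 0.807 | 0.939 | 0.667 | 0.843 |
| 0.5 | 0.807 | 0.904 | 0.807 | 0.904 |
| 0.7 | 0.807 | 0.866 | 0.955 | 0.977 |
| 0.8 | 0.807 | 0.846 | 0.994 | 0.997 |

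With the t distribution the score-SD figures at rho 0.3, 0.5 and 0.7 are 0.662, 0.804 and 0.953 against 0.839, 0.901 and 0.976, which is half a point lower at most. A simulation of 4,000 trials per rho agrees: 0.665, 0.804 and 0.958 against 0.837, 0.895 and 0.981.

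**4. Total completers for 80% power, at rho 0.3, 0.5 and 0.7.**
- d on the change SD: 198 for the change score; 128, 148 and 168 for ANCOVA.
- d on the score SD: 276, 198 and 118 for the change score; 180, 148 and 102 for ANCOVA.

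**5. Follow-up, assuming one common correlation across all four visits.** The mean of T1–T3 has variance (1 + 2rho)/3. Its covariance with T0 is rho, so adjustment leaves (1 + 2rho)/3 − rho². At rho 0.3, 0.5 and 0.7 this is 0.443 of 0.533, 0.417 of 0.667, and 0.310 of 0.800, giving ratios of 0.83, 0.63 and 0.39. The T3 − T1 contrast has covariance rho − rho = 0 with T0, so adjustment does not change its variance. T0 therefore sharpens the overall arm effect but not arm-by-time.

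**The case against.** The strongest reply is that nothing here is an error. Under randomisation a between-arm t-test on changes is unbiased and holds its type I error. A reader might infer that chance baseline imbalance makes the result invalid. It does not: at 100 per arm the standard error of the baseline difference is √(2/100) = 0.14 SD, and a one-standard-error imbalance at rho 0.5 moves the change contrast by 0.5 × 0.14 = 0.07 SD, averaging zero over randomisations. This part of the reply stands.

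A reader might also infer that the trial misses its 80% power. On the change-SD reading it meets that target at every rho. It falls short only if d is on the score SD and rho is below 0.5, and the article settles neither. At rho 0.8 the gain is modest. This stands too.

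On follow-up, the stated purpose of the ANOVA is stability, which is the question that T0 helps little. A reader might infer that the analysis will be confined to a small, selected group of complete cases. A classical mixed ANOVA does need all three visits, but that follows from the named method and not from anything the article says about missing data, whose handling may sit in an unseen plan. The article gives no loss rate after T1, and its 200 completers may mean completers through T3. The Discussion says only that treatment dropout might be a primary limitation. Nor can a mixed model recover students with no post-baseline data, such as those excluded for missed deadlines.

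Lastly, Section 2.8 introduces the between-arm test as an addition to the test of change against zero, so it should not be called the plan's designated primary test.

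What survives is that the article names its test, T0 is available, and ANCOVA is more precise under either reading of d.

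**Conclusion.** The point holds as avoidable loss of efficiency. It is not bias, and it is not a demonstrated failure to reach the planned power. For any rho below 1 with equal SDs, the planned test is less precise than ANCOVA. At rho 0.3 to 0.7 the ANCOVA variance is 65% to 85% of the change-score variance. In power terms the gain is about 6 to 13 percentage points if d is on the change SD, and about 2 to 18 points if it is on the score SD. The size depends on rho and on the scale of d, which the article leaves open; the direction does not. For follow-up, the gain from T0 is confined to the arm effect. The change is worth making because it needs no new data.

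**What to change.** - **T1:** for each outcome, make the between-arm test a linear model of the T1 score on arm and T0 score, with its Bayesian counterpart. Report the adjusted arm difference with its 95% confidence interval.
- **Follow-up:** use a linear mixed model of T1, T2 and T3 with arm, time, arm-by-time and T0 score as a covariate, on all available observations. Keep the arm-by-time test for the stability question.
- **Sample size section:** state which SD scales d = 0.40.

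**Cost:** no extra visits, measures or participants. Beyond the analysis wording, the Bayesian part needs work: the priors and the design analysis in Section 2.7 are set on d for an unadjusted two-group comparison, and would have to be restated and rerun on the adjusted effect.

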We expect to have enough data to tune a model that highlights treatment response predictors and different trajectories in students’ response to treatment. We will test five different algorithms: Linear Discriminant Analysis (LDA); Classification and Regression Trees (CART); k-Nearest Neighbors (kNN); Support Vector Machines (SVM) with a linear kernel; and Random Forest (RF). This will offer a good mixture of simple linear (LDA), non-linear (CART, kNN), and complex non-linear methods (SVM, RF).

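### The plan says outcomes must be dichotomised before they can be prediction targets; this is untrue for four of its five algorithms and, under normality, costs at least 36% of the information on predictors of change.

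*Protocol article*

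**What the plan says.** The fourth hypothesis (Aims and Hypotheses) is that "the large amount of collected data will allow the identification of predictors of treatment response and different trajectories in treatment response". Section 2.7 repeats the expectation, "We expect to have enough data to tune a model that highlights treatment response predictors and different trajectories in students’ response to treatment", and lists five algorithms: "Linear Discriminant Analysis (LDA); Classification and Regression Trees (CART); k-Nearest Neighbors (kNN); Support Vector Machines (SVM) with a linear kernel; and Random Forest (RF").

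Section 2.8 gives the purpose: "we will explore the possibility to use ML algorithms to tune a model able to predict the responders on each of the primary outcomes". It then states as a general rule: "Before entering an outcome measure as a target variable (i.e., to be classified/predicted variable), variables have to be dichotomized". A responder is a participant with "a change larger than 1 standard error of the mean (SEM) calculated on the baseline distribution". On evaluation, "A total of 20% of the data will be held out for testing purposes", with one fixed split for all algorithms and outcomes.

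On sample size, section 2.7 says "we will recruit 260 students to obtain 200 study completers". The protocol article gives no expected responder share, mean change or T0–T1 correlation, and describes no model with a continuous target.

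**The concern.** The prediction targets are changes on multi-item scales such as the BDI-II, STAI, PSQI and SBI. The plan turns each into a yes/no label and presents this as something the methods demand. The reference to a minimum clinically important difference explains where the cut goes. It does not explain why a cut is needed before modelling.

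Wherever the cut is placed, a student who just passes it is treated the same as one who improves greatly, and a student who just misses it the same as one who deteriorates. That discards the size of the change, which is what a search for predictors and trajectories of response needs. What is at stake is the fourth hypothesis: with a modest training set, real predictors become harder to find because of a step the algorithms do not need.

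**Working it through.** **1. The plan's own figures.** Section 2.7 gives d = 0.40, 80% power and two-sided alpha 0.05.
- Per arm: 2 × (1.960 + 0.842)² / 0.40² = 98.1, so 99 per arm or 198 in total. The exact t-test gives 99.1 per arm, and power 0.804 at 100 per arm. The 200 completers are reproduced.
- Attrition: 60/260 = 23.1%, which takes 200 to 260.
- Training set: 80% of 200 completers = 160 records.

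**2. Is a class target required?**

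| Algorithm | Regression form? |
|---|---|
| LDA | No; needs classes |
| CART | Yes; regression trees are part of the name that section 2.7 spells out |
| kNN | Yes; average of the neighbours' outcomes |
| SVM, linear kernel | Yes; support vector regression |
| RF | Yes; regression forest |

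The stated necessity is false for four of the five.

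**3. Information lost by any cut.** For a normal outcome and a weak linear predictor, the efficiency of a binary target relative to the continuous one is φ(z)² / [p(1 − p)], where p is the responder share and z = Φ⁻¹(p). It is greatest at p = 0.50, where it equals 2/π = 0.637. The smallest possible loss is therefore 1 − 0.637 = 36%. At other shares:

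| Responder share p | Efficiency | Loss |
|---|---|---|
| 0.50 | 0.637 | 36% |
| 0.30 or 0.70 | 0.576 | 42% |
| 0.21 or 0.79 | 0.501 | 50% |
| 0.10 or 0.90 | 0.342 | 66% |

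**4. The planned cut.** Assumptions not in the document: normal change scores, T0–T1 correlation 0.6, mean improvement 0 to 0.8 SD of change.
- One standard error of the mean with n = 200: 1/√200 = 0.071 baseline SD.
- SD of change: √[2(1 − 0.6)] = 0.894 baseline SD.
- Cut in SD of change: 0.071/0.894 = 0.079.
- Responder share: p = Φ(mean − 0.079).

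| Mean improvement (SD of change) | p | Efficiency | Loss | 160 records act like |
|---|---|---|---|---|
| 0 | 0.47 | 0.635 | 36% | 102 |
| 0.25 | 0.57 | 0.630 | 37% | 101 |
| 0.50 | 0.66 | 0.597 | 40% | 95 |
| 0.80 | 0.76 | 0.526 | 47% | 84 |

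**5. Sensitivity.** Here mean change is in baseline SD.
- With correlations of 0.3 to 0.7 and the same n = 200 cut, a mean change of 0.8 gives losses of 45% to 54%, and a mean change of 1.0 gives 49% to 63%.
- If SEM is instead read as the standard error of measurement, with assumed reliability 0.8 to 0.9, losses run from 36% to 52% over mean changes of 0 to 1.0.

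The 36% floor holds throughout under normality. The upper end depends on how unbalanced the responder share turns out to be.

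**The case against.** The strongest defence is that the sentence has a context. The declared aim is to predict responders, the panel includes LDA, and one fixed hold-out is used so that performances can be compared. For all five methods to share one target, that target must be a class. The work is also labelled exploratory. All of this stands. It makes a binary target a legitimate choice, and it is why the responder classification and LDA should be kept. It does not make dichotomisation necessary, nor does it explain why the only models offered for the fourth hypothesis should discard the size of the change.

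Three stronger readings might be inferred, and the document does not support them.
- **That all the outcome analyses are dichotomised.** The rule covers only the targets of the predictive models. The other scales enter as predictors with no statement that they are cut, and the t-tests and mixed ANOVAs in section 2.8 use the scores themselves.
- **That the loss is a known range ending at 50%.** No responder share is given. The 36% is a floor under normality, and 50% is merely the value at about 21% or 79% responders, not a ceiling.
- **That the loss can be stated as a fall in power for the planned models.** The plan trains and tests classifiers; it does not test single predictors at 0.05. The d = 0.40 is a between-group treatment effect, and nothing in the document makes it the effect of a predictor.

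**Conclusion.** The point holds for the targets of the exploratory predictive models. The claim that they must be dichotomised is wrong for CART, kNN, SVM and RF. Under normality and a weak linear predictor, following it loses at least 36% of the information on predictors of change. The loss is about 36% to 47% with the planned cut under the assumptions in step 4, and more if the responder share is more unbalanced. About 160 training records then carry the information of about 84 to 102.

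This weakens the fourth hypothesis and the expectation of having enough data. It does not touch the comparison of the intervention with the control condition. It is a cheap improvement to an exploratory aim, not a threat to the trial.

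**What to change.** In section 2.8:
- Delete the statement that dichotomisation is required.
- Prespecify continuous-target models, with the T0–T1 change or the T1 score as target. Use the regression forms of CART, kNN, SVM and RF, plus a linear regression as the simple linear method.
- Fit them on the same fixed 80/20 split and judge them by out-of-sample R-squared or mean absolute error.
- Name these models as the ones used to identify predictors for the fourth hypothesis.
- Keep the responder classification, including LDA, alongside, and describe it as a choice that serves the aim of predicting responders.

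The cost is a wording change, some extra model fitting and a second performance measure to report. No new data are needed.
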